##### Blinding

Given the nature and complexity of intervention & its delivery, it will not be possible to completely blind or conceal the intervention from the teachers, students, and field-staff. The trial will be open-label. Nonetheless, the study-statistician will be blinded till the database is locked for final-analysis.

##### Student-recruitment

Enrolment will start after obtaining assent and parental-consent from the eligible students. In the case of multiple sections with > 60 students in each grade, one section will be randomly selected from each grade. The intervention will be provided to all students in the selected grades irrespective of their number. The teachers will be free to provide intervention for other sections, but data will not be collected.

##### Intervention-schools

For the schools randomised to the intervention arm, the teachers nominated by their designated superior officials will be trained on the curriculum resource guide content in a 3-day workshop. The teachers who provide consent to participate in the research, complete the training, stay in the selected-schools for the study period and deliver the intervention will be selected. Following baseline assessment of participating students, the trained teachers will then proceed with the implementation of SUMS Intervention Curriculum Resource Guide, which requires approximately 10–15 h of classroom time over two months. In the intervention delivery, the teachers will be given pedagogical flexibility but will be instructed to adhere to the standardised core content, recommended lesson plans and procedures to maintain fidelity (Table 2). Booster sessions will be provided at 2-months and 5-months following the initial intervention.

**Table 2 Tab2:** Quality assurance and data management

**Field-team:** The field-team will comprise of Project-Assistant who will be trained in standard protocols of questionnaire administration for data collection, coordinate with local stakeholders, monitor compliance of intervention protocol and its deviations and also conduct public-engagement activities.	
**Post-recruitment retention strategies:** For the Project-Assistant, all the activities required to achieve the trial goals will be communicated clearly. A weekly meeting will be held to sort out the field related issues. In addition, the teachers, principals, and other key stakeholders will be informed on the trial’s status and progress through newsletters.	
**Trial-Monitoring:** The Project-Assistant will check for intervention-delivery, protocol-adherence, data-collection and reporting using supervisory check-list during their monthly visits. Principal-Investigator will review this monthly visit reports during monthly review meetings. The central-research team (comprising of Principal-Investigator and other expert-collaborators) will have meetings once in 6 months at NIMHANS to review the progress, work plan, discuss and troubleshoot any unresolved field issues. A register will be maintained for all review meetings. Constant support will be obtained from the expert collaborators through tele-meetings. A Trial Steering Committee (TSC) and Data Safety Monitoring Board (DSMB) will be constituted independently of the research team, the members of whom will have no conflict of interest. The TSC will comprise experienced experts to oversee the trial and independently evaluate the trial to monitor progress, intervention delivery, protocol adherence and data management. A three-member DSMB will monitor the data as the trial progresses to identify any emerging safety concerns for the study participants and problems in the study’s conduct. DSMB will decide on the continuation of trial following interim analysis.	
**Intervention Fidelity:** Teachers will be encouraged to fill a protocol-adherence checklist. The educational-intervention delivered by the teacher will be audio-recorded to assess fidelity of intervention delivery. A random sample of audiotaped sessions will be evaluated for each teacher using fidelity checklists for intervention-delivery based on the standardised core content of the SUMS intervention curriculum resource guide. Feedback will be provided to support the booster-training sessions. Our fidelity assessment will also incorporate feedback and recommendations of the independent evaluation and reports of supervisory-checklist.	
**Data Management:** The study will have meaningful engagement with key stakeholders across all study phases. All data stored securely in-line with our data-management protocol will protect the confidentiality of participants. Any personal identifiers of study participants will be removed before analysis. Audiotapes and transcripts containing participants identity (if any) will be destroyed post-analysis of data. Participant’s identity will not be revealed in any of the publications related to this research. The principal investigator will have access to the final trial dataset.	

##### Control-schools

Control-schools will continue to provide regular teaching as usual of the existing course to their students. The control group will receive the interventions at the end of the 12-month follow-up assessment in intervention-schools. The teachers in the waitlist control arm will be trained just one month before their scheduled intervention to prevent contamination.

##### Parental-consent

An information letter detailing the intervention program and data collection along with consent-form will be sent to the parents/guardians of participating class for parental-consent. Parental-consent will be recorded with a signature/thumbprint. Existing school communication channels (letter, diary or parent’s teachers meeting) will be used to maximise the parental-consent for child participation. Parents will be provided an opportunity to contact the field-team to discuss the study and their participation. An attempt will be made to meet the non-responding parents to obtain their consent. Children without parental consent in the selected class will be permitted to attend intervention sessions, but data will not be collected from them.

##### Discontinuation-criteria

The students may withdraw their participation at any point in time during the study. An attempt will be made to document the reasons for withdrawal.

##### Timing of outcome-measurement

Data will be collected using self-administered questionnaire. Students will complete the survey during class time in the presence of trained project assistant/ teacher to assist the children with reading, writing and answering any queries. Data will be collected at 4-timepoints from both intervention and control schools: baseline and 6-weeks, 6-months and 12-months post-intervention (Fig. 2). To maximise data completeness, all effort will be made to obtain data from absentee students through liaison with key school-staff.

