### Intervention

**SUMS intervention (MHP + MHL + MH-FA)** is a classroom-based teacher-led integrated school mental health intervention that will promote positive mental health, mental health literacy and behaviours for First Aid in Mental Health among school-going adolescent school children. As described earlier, SUMS intervention takes the form of a classroom-ready resource (the curriculum resource guide) designed to be delivered by usual classroom teachers to students in grades 6 and 7 (ages 12 to 15 years). The curriculum resource guide contains 10 modules categorised under 3 units (Mental Health Promotion, Mental Health Literacy and First Aid in Mental Health). The ten modules are as follows: Positive mental health, Promoting Resilience, Promoting Mindfulness, Life Skills Education, Mental Health Literacy, Understanding Mental Health and Mental Illness, Stigma of Mental Illness, Information on specific mental illnesses, seeking help and finding support, First Aid in Mental health and strategy for mental health first Aid (Table 1). Each module’s purpose is to provide teachers with classroom-ready lesson plans, activities, and easily accessible resources. The ten modules are designed to be taught in sequence and are intended to be delivered on the usual school days through 10–15 h of classroom time.

**Table 1 Tab1:** SUMS Intervention-Curriculum framework

Units	Module	Teaching method
Mental Health Promotion (MHP)	Module 1: Positive mental health Module 2: Promoting Resilience Module 3: Promoting Mindfulness Module 4: Life Skills Education	Educational session followed by Participatory and experiential activities as recommended in the resource guide (Interactive discussions, Group discussion, Co-operative play, Storytelling. Role play, Brainstorming, Debate, within-school competitions, wall-magazine, etc.,)
Mental Health Literacy (MHL)	Module 5: Understanding Mental Health and Mental Illness Module 6: Stigma of Mental Illness Module 7: Information on specific mental illnesses Module 8: Seeking help and finding support	
First Aid in Mental Health (MH-FA)	Module 9: First Aid in Mental health Module 10: Strategy for First Aid in Mental health	

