#### Primary outcome

The primary outcome, **Positive mental health literacy** will be measured using a 10-item Mental Health-Promoting Knowledge (MHPK-10) scale. It is a valid and reliable one-dimensional instrument measuring knowledge of factors promoting good mental health among adolescents. The MHPK-10 had demonstrated good internal validity and test-retest reliability (r = 0.74) among adolescents. For each item, respondents rate items on 1–5 likert-type scale, the extent to which they are correct or wrong. The score range is 10–50, with a higher score indicating a higher positive mental health literacy [26].

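### The teacher who delivered SUMS may help pupils with the knowledge questionnaire, and control teachers could be trained before their own pupils' 12-month survey; either could bias the arm difference

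*Protocol article*

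**What the plan says.** All places are in the protocol article.

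- **Survey help** (Timing of outcome-measurement): questionnaires are self-completed in class time, "in the presence of trained project assistant/ teacher to assist the children with reading, writing and answering any queries". Both arms are surveyed at baseline, 6 weeks, 6 months and 12 months.
- **Delivery** (Intervention): the curriculum guide is "designed to be delivered by usual classroom teachers to students in grades 6 and 7".
- **Primary outcome** (Primary outcome): on MHPK-10, "respondents rate items on 1–5 likert-type scale, the extent to which they are correct or wrong".
- **Blinding** (Blinding): "it will not be possible to completely blind or conceal the intervention from the teachers, students, and field-staff". The one safeguard named there is that "the study-statistician will be blinded till the database is locked for final-analysis".
- **Training for data collection** (Table 2): the project assistant will be "trained in standard protocols of questionnaire administration for data collection". Table 2 says nothing comparable about teachers.
- **Waitlist timing** (Control-schools): "The control group will receive the interventions at the end of the 12-month follow-up assessment in intervention-schools", and control teachers are "trained just one month before their scheduled intervention to prevent contamination".

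**The concern.** There are two separate routes to bias.

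**Help at the survey.** A teacher who has just taught the SUMS content may be the adult answering questions while pupils mark statements on that content as right or wrong. That teacher knows the arm, and his or her sessions are recorded and scored for fidelity (Table 2). A control-school teacher in the same role has not had SUMS training, at least until the waitlist phase. The same permission could therefore produce different help in the two arms. Help that favours the intervention arm would inflate the MHPK-10 difference at any of the three follow-up surveys. Blinding the statistician cannot undo this, because it enters when the data are captured.

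**Training of control teachers.** The waitlist schedule refers to the 12-month assessment in the intervention schools, not to each control school's own survey. If control teachers learn the content before their pupils are surveyed, they could pass some of it on, through help at the survey or in ordinary class contact. Control scores would rise and the 12-month difference would shrink.

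**Working it through.** **1. Can the delivering teacher be the helper?** Four statements bear on this:

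| Question | Section | Answer |
|---|---|---|
| Who helps? | Timing of outcome-measurement | Project assistant or teacher; queries not limited by content |
| Who delivers SUMS? | Intervention; Intervention-schools | Usual classroom teachers |
| Who knows the arm? | Blinding | Teachers, students and field staff |
| Who is trained to administer questionnaires? | Table 2 | Project assistant |

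The survey is held in class time, so the usual classroom teacher is an obvious candidate. The text permits this and no sentence rules it out. It does not say that it will happen.

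**2. When are control teachers trained?** Let E be the end of the 12-month assessment in intervention schools, S the start of control delivery, T the training of control teachers, and C the end of a control school's own 12-month survey. The article gives T = S − 1 month, with S following E. Training comes after the control survey only if T ≥ C, that is S ≥ C + 1 month. Assume the two arms are surveyed together, so E and C are both about month 12:

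| Gap between survey and control delivery (assumed) | S | T | Training after the control survey? |
|---|---|---|---|
| none | 12 | 11 | no |
| half a month | 12.5 | 11.5 | no |
| one month | 13 | 12 | yes, just |

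The article states no gap.

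**3. The plan's own sample-size figure.** Inputs from Sample size and power: 4 schools per arm, 50 pupils per school, ICC 0.01 to 0.05, two-sided 5% level, 85% power, standardised difference 0.37 to 0.56. The design effect is DE = 1 + (50 − 1) × ICC.

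- ICC 0.01: DE = 1.49; 132 × 1.49 = 196.7 per arm, 393 in total.
- ICC 0.05: DE = 3.45; 58 × 3.45 = 200.1 per arm, 400 in total.

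The stated 400 reproduces and is not in dispute here.

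**4. How sensitive is the comparison to such a bias?** This is an illustration only: the article gives no bias size, so b (in SD units) is assumed at 0.05, 0.10 and 0.20. The standard error is √(2 × DE / 200), which is √0.0149 = 0.122 at ICC 0.01 and √0.0345 = 0.186 at ICC 0.05. The normal reference that reproduces the plan's figure is kept.

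- Help favours the intervention arm and there is no true effect: error rate = 1 − Φ(1.96 − b/SE) + Φ(−1.96 − b/SE).
- Control scores are raised by b: power at a true difference of d − b.

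| b (assumed) | Error rate, ICC 0.01 | Error rate, ICC 0.05 | Power, d = 0.37, ICC 0.01 | Power, d = 0.56, ICC 0.05 |
|---|---|---|---|---|
| 0 | 5% | 5% | 86% | 85% |
| 0.05 | 6.9% | 5.8% | 75% | 78% |
| 0.10 | 13.0% | 8.4% | 60% | 70% |
| 0.20 | 37.4% | 19.0% | 29% | 49% |

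The table shows what a bias of a given size would do. It does not show that one of that size will occur.

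**The case against.** The best defence is that the article describes a possibility and already has safeguards. The word trained may cover the teacher as well as the project assistant. The assistant may help in both arms. Adverse-events promises privacy while forms are filled in, and Table 2 has data collection checked with a supervisory checklist and reviewed monthly. Detailed helper instructions usually sit in a field manual. On timing, the late training of control teachers is itself meant to prevent contamination, delivery at the end of an assessment need not mean the same day, and Fig. 2, which is not shown here, may display the order.

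Much of this stands, and it rules out several stronger readings that a reader might infer:

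- *Help does differ by arm because control helpers are untrained.* The article does not say so. It names the same kinds of helper for both arms, so help could differ.
- *The protocol schedules control training before the control survey, or contradicts itself.* It does not. The two sections are compatible if control delivery starts at least a month after the control survey.
- *The trial's result will be inflated.* At 12 months the two routes would tend to act in opposite directions, so the net direction there is unknown.
- *The bias can never be separated from the effect.* That is too absolute. Intervention teachers may already be trained by baseline, so some helper influence could show in baseline scores, and the model uses repeated measures. Nothing ensures, however, that the same helper gives the same help at each round.
- *A teacher's presence will distort the stigma and distress answers between arms.* A teacher could be present in both arms, and presence alone need not create an arm difference.

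What the defence does not answer is that neither the privacy promise nor the checklist keeps the delivering teacher away from the questionnaire, and no sentence puts the control survey before control training. Allowing a teacher to answer queries is a rule that the article states, not a detail it leaves out.

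**Conclusion.** The point holds as a risk that the current wording permits and that can be avoided. The unblinded delivering teacher is not barred from answering questions during the primary-outcome test, so help could differ by arm and bias the MHPK-10 difference. Control teachers could be trained at about month 11, before or during their own pupils' 12-month survey, which could shrink the difference at that survey only. This second part assumes that the arms are surveyed at about the same time and that control delivery follows with less than a month's gap.

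The size of either bias cannot be estimated from the document. Under assumed biases of 0.05 to 0.20 SD, the 5% error rate would become 5.8% to 37.4%, or the planned power of about 85% would fall to between 78% and 29%, depending on the ICC and the target difference. The change should be made before recruitment, which the article reports as not yet begun. It does not call the sample size into question.

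**What to change.** 1. **Timing of outcome-measurement:** state that in both arms the project assistant, who is already to be trained in questionnaire administration, gives all help under the same script. The script allows help with reading and writing and no explanation of content. A teacher who delivers, or will deliver, SUMS neither assists nor sees answers.
2. **Control-schools:** state that no teacher in a control school is trained until that school's own 12-month questionnaires are collected. Bring the matching statements in the abstract and under Randomisation into line.

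**Cost.** The project assistant must attend every survey sitting: at least 8 schools × 4 rounds = 32 visits. If grades 6 and 7 sit separately this becomes 32 × 2 = 64 sittings, and revisits for absentees add more. With fewer adults to help, weak readers may need more time, which should be allowed for so that completion does not suffer. Keeping the one-month interval between training and delivery means the control arm starts about one month later than if delivery began when the 12-month assessment ends. The sample size and the analysis model need no change.

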**Fig. 2 Fig2:**
[figure not shown]
Trial process. MHPK: Mental Health Promoting Knowledge; MHLS: Mental Health Literacy Scale; PMHSS: Peer Mental Health Stigmatization Scale; RIBS: Reported and Intended Behaviour Scale; IASMHS: Inventory of Attitudes towards Seeking Mental Health Services; K6: Kessler psychological distress scale; CD-RISC: Connor-Davidson Resilience Scale; MH-FA: First Aid in Mental Health. *Exploratory outcomes include academic achievement, absenteeism, educational stress, suicidality, bullying and substance use

##### Adverse-events

We do not anticipate any risk to the participating students due to our interventions. However, potential discomfort due to sensitive questions of survey assessment related to self-perception and well-being cannot be ruled out when answering in the classroom. Due-care will be taken to ensure the privacy and confidentiality of students while filling the survey forms. A register & form will be maintained to record unexpected severe events during the trial. Any students who require professional mental help during the study will be referred to the district mental health team for further management.

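### The adverse-event register covers events that are both unexpected and severe, so it leaves out survey discomfort, the one risk its own section names, and also expected serious reactions and referrals

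*Protocol article*

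**What the plan says.** Four statements in the Adverse-events section of the protocol article matter here.

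- On the intervention: "We do not anticipate any risk to the participating students due to our interventions".
- On the assessments: "potential discomfort due to sensitive questions of survey assessment related to self-perception and well-being cannot be ruled out when answering in the classroom". The section adds that care will be taken over privacy while the forms are filled in.
- On recording: a register and form "will be maintained to record unexpected severe events during the trial".
- On follow-up: "Any students who require professional mental help during the study will be referred to the district mental health team for further management". Neither this section nor any other says that these referrals are logged.

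Table 2, under Intervention-schools, describes the oversight. On site monitoring: "The Project-Assistant will check for intervention-delivery, protocol-adherence, data-collection and reporting using supervisory check-list during their monthly visits". On independent safety review: "A three-member DSMB will monitor the data as the trial progresses to identify any emerging safety concerns for the study participants". The Stopping-rule section gives a futility criterion.

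**The concern.** The section identifies a risk and, in the same paragraph, sets up a record whose entry rule does not admit that risk. This is not a definition left to a fuller document. The article states the register's scope, and that scope does not match the text around it.

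Two things are at stake. First, the register is the only event-level safety record the article describes. If it is what the DSMB sees, the DSMB sees an incomplete account. Second, an empty or nearly empty register at the end of the trial could be reported as showing that the assessments were well tolerated, although it was never set up to record the reaction in question. The participants are schoolchildren who answer questions on distress and suicidal ideation in a classroom, so a reader of the results will want to know how they reacted.

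**Working it through.** The article states no adverse-event figure, so there is nothing to reproduce. The check applies the entry rule to the kinds of event the document mentions or implies, then asks whether other data fill the gap.

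**Step 1. Apply the rule: unexpected and severe.**

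| Event | Unexpected? | Severe? | Enters the register as worded? |
|---|---|---|---|
| Discomfort over sensitive questions | No, foreseen in the same section | Ordinarily not | No |
| A foreseen reaction that becomes serious | No, if treated as the foreseen kind | Yes | No |
| Non-severe distress in a SUMS session | Yes, since no risk from the intervention is expected | No | No |
| Referral to the district mental health team | Not a criterion | Not a criterion | Only if the underlying event meets both conditions |
| An unexpected severe event of any kind | Yes | Yes | Yes |

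The first four rows are the gap. The last row shows that the register is not empty by design.

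**Step 2. Ask what the other data sources can show.**

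- *K6 (Psychological distress) and suicidal ideation (Exploratory outcomes).* Timing of outcome-measurement sets four timepoints in both arms. These outcomes can reveal a harmful effect of the intervention. They cannot readily show distress caused by the survey, because both arms take the same survey and a common effect largely cancels in the comparison.
- *Withdrawal reasons (Discontinuation-criteria).* Documentation is only attempted, and covers only pupils who withdraw.
- *Monthly supervisory checklist (Table 2).* Four areas are listed: delivery, adherence, data collection and reporting. Distress and referrals are not named.
- *Interviews (Process evaluation).* These take place in the final stages and are meant to explore implementation and context.
- *DSMB (Table 2, Interim-analyses).* It has a general duty to watch for safety concerns and receives the 6-week analysis. No event-level source other than the register is described.

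These sources limit the gap for harm caused by the intervention. None provides a systematic record of survey-related distress or of referrals.

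**Step 3. Size.** With the planned 400 pupils (Sample size and power) and four surveys, and no losses, there are 400 × 4 = 1,600 questionnaire sittings at which the named risk could arise. The article allows for a 5% loss to follow-up, so the number completed may be lower. It gives no rate of distress or referral, so the sittings cannot be turned into a count of missed events.

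**The case against.** The strongest case against has four parts.

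*Harm can show elsewhere.* Unexpected severe events are recorded, distress and suicidal ideation are measured in both arms, withdrawal reasons are sought, and a DSMB watches for safety concerns. This stands. A reader might infer from the narrow register that the trial is bound to report no harm, or that the DSMB has nothing usable. The document supports neither: the record is incomplete, not empty, and the DSMB also receives outcome data.

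*The named risk belongs to the survey, not to SUMS.* Both arms take the survey, so leaving mild discomfort off the register does not in itself conceal harm caused by the intervention. This also stands. The point concerns complete safety recording more than bias in the treatment comparison. A marked breakdown might moreover be judged to go beyond discomfort and be entered as unexpected and severe. That would depend on the recorder's judgement, because the wording does not settle it.

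*Unequal reporting between arms is not shown.* The trial is open-label, and only intervention teachers are trained during the comparison period, so a reader might infer that events will be reported more readily in SUMS schools and that no comparison of harms could be interpreted. That is speculation. Nothing restricts the monthly visits to intervention schools, two of the four checklist areas apply equally to control schools, and the article states no comparison of register entries between arms.

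*This is a condensed article.* Form fields and reporting schedules may well be in the full protocol, and their absence here is no fault. That covers operational detail. It does not cover a scope that the article states and that conflicts with its own paragraph.

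**Conclusion.** The point holds in a limited form. As worded, the register omits the only risk the Adverse-events section names, expected serious reactions, and referrals as such. The event record may therefore understate harms, and an empty register could not be read as reassurance about survey-related distress. The size in events is unknown.

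The conclusion rests on two assumptions. One is that the wording means both conditions must be met and that no second register exists; the article mentions none. The other is that the register is the event record the DSMB would use; the article does not say so, but describes no other. The change is worth making, but the point does not threaten the primary analysis. Trial status and review anticipates recruitment only after March 2022, so on the article's timetable the wording could be settled before enrolment.

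**What to change.** In the Adverse-events section, replace the register's scope with three categories:

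- distress observed or reported during or after a survey or a SUMS session;
- any referral to the district mental health team;
- any serious event, whether expected or not.

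Use the existing form, complete it in the same way and on the same schedule in intervention and control schools, and tabulate the entries by arm for the DSMB. The change concerns what is recorded, not how pupils are managed.

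The cost is a reworded definition and a little more recording time. A trained project assistant or teacher is already present at each survey, and the Project-Assistant already makes monthly visits. The reported event count will be higher than under the present wording, and the report should say that this reflects the wider definition.
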